## Abstract

**Background:**

HIV transmission can be decreased substantially by reducing the burden of undiagnosed HIV infection and expanding early and consistent use of antiretroviral therapy (ART). Treatment as prevention (TasP) has been proposed as key to ending the HIV epidemic. To activate TasP in high prevalence countries, like South Africa, communities must be motivated to know their status, engage in care, and remain in care. Community mobilization (CM) has the potential to significantly increase uptake testing, linkage to and retention in care by addressing the primary social barriers to engagement with HIV care—including poor understanding of HIV care; fear and stigma associated with infection, clinic attendance and disclosure; lack of social support; and gender norms that deter men from accessing care.

**Methods/design:**

Using a cluster randomized trial design, we are implementing a 3-year-theory-based CM intervention and comparing gains in HIV testing, linkage, and retention in care among individuals residing in 8 intervention communities to that of individuals residing in 7 control communities. Eligible communities include 15 villages within a health and demographic surveillance site (HDSS) in rural Mpumalanga, South Africa, that were not exposed to previous CM efforts. CM activities conducted in the 8 intervention villages map onto six mobilization domains that comprise the key components for community mobilization around HIV prevention. To evaluate the intervention, we will link a clinic-based electronic clinical tracking system in all area clinics to the HDSS longitudinal census data, thus creating an open, population-based cohort with over 30,000 18–49-year-old residents. We will estimate the marginal effect of the intervention on individual outcomes using generalized estimating equations. In addition, we will evaluate CM processes by conducting baseline and endline surveys among a random sample of 1200 community residents at each time point to monitor intervention exposure and community level change using validated measures of CM.

**Discussion:**

Given the known importance of community social factors with regard to uptake of testing and HIV care, and the lack of rigorously evaluated community-level interventions effective in improving testing uptake, linkage and retention, the proposed study will yield much needed data to understand the potential of CM to improve the prevention and care cascade. Further, our work in developing a CM framework and domain measures will permit validation of a CM conceptual framework and process, which should prove valuable for community programming in Africa.

**Trial Registration:**

NCT02197793 Registered July 21, 2014.

## Background

In 2014, UNAIDS established targets in hopes of reaching the end of the HIV epidemic by 2030. The targets dictate that by 2020, 90% of all people living with HIV should know their HIV status, 90% of all people with diagnosed HIV infection will receive sustained antiretroviral therapy (ART), and 90% of all people receiving ART will achieve viral suppression [1]. This 90-90-90 framework was largely the result of ground breaking research demonstrating that HIV transmission can be decreased substantially by reducing the burden of undiagnosed HIV infection and expanding early and consistent use of ART. [2, 3] Treatment as prevention (TasP), or treating an HIV-positive person with ART to reduce their HIV viral load and thus reduce the risk of forward transmission of the virus to a negative partner, is the key to ending the HIV epidemic [4, 5]. In high HIV prevalence countries like South Africa (adult national HIV prevalence estimated at 16.9%) [6, 7], observational studies have demonstrated that residents of communities with greater ART coverage have a lower risk of HIV acquisition [8].

To activate TasP in high prevalence settings and reach 90-90-90 targets, communities must have access to HIV testing and treatment and also be motivated to know their status, engage in care if they test HIV positive, and remain in care, including medication adherence to ensure viral suppression. Currently uptake of testing, linkage to care, and treatment falls short of that needed to significantly decrease new infections, despite widespread availability of HIV testing and care services. National data from South Africa indicated that in 2012 while 65.0% of the population reported ever testing for HIV, with approximately 40% having tested in the last year, only 37.8% of HIV-positive men and 55.0% of HIV-positive women knew their HIV status [9]. Though South Africa has the largest ART program in the world, only an estimated 52% of eligible patients are on treatment [10], and only an estimated 31% of those living with HIV have initiated treatment [7]. Furthermore, population-based data from rural areas in the North West province in 2014 indicate that less than half of those on ART are virally suppressed [11]. At current rates of testing and treatment coverage, South Africa will fall far short of meeting the 90-90-90 goals.

Primary barriers to testing uptake and engaging in HIV care are related to social and structural factors that shape clinical care seeking—these include HIV-related stigma and fear of disclosure, fears around treatment side effects, male gender norms that discourage men from engaging in care, and a general lack of community awareness about the benefits of HIV care and treatment [12]. HIV-related stigma leads to delays in HIV testing and treatment as well as poor adherence to clinic visits and medication [13–16]. Similarly, fear of ART side effects and misconceptions around the benefits of early diagnosis, care and treatment can keep people who are living with HIV/AIDS (PLWHA) out of care [17, 18]. Finally, gender norms are a major social barrier for testing, linkage to care and treatment for men, as traditional gendered conceptualizations dictate that it is unmasculine to seek care, resulting in men accessing health care services at lower rates than women [19–22]. Men also access ART at a far lower rate and at more advanced stages of disease compared to women [23–27].

Tackling social barriers to HIV prevention, testing and linkage to care, requires building a sustained, community-wide response [28]. Community mobilization (CM) has significant potential to improve testing uptake and linkage to and retention in care by addressing the social barriers to engagement with HIV care [12, 29, 30]. There is strong evidence that CM can improve behavioral outcomes, such as consistent condom use, by addressing discrimination, creating social cohesion, and extending social participation and networks for target communities [28, 31–38]. CM has successfully changed inequitable gender norms through engaging men to question traditional masculinity and support each other to change social inequalities [37, 39–43]. In the large Project Accept trial, CM markedly improved HIV testing uptake by changing community norms around HIV testing through enhanced community participation, raising community awareness, and partnership building [44, 45]. UNAIDS has designated CM as a critical enabler—or an activity that is necessary to support the effectiveness of programs. [46] Despite this, CM strategies for linkage to and retention in HIV care have not been rigorously defined or evaluated, with few conceptual frameworks that provide a theoretical basis for program design. In fact, few interventions have improved linkage to and retention in HIV care in resource poor settings, despite the urgent need [47–49].

To address this gap in interventions to improve linkage to and retention in HIV care on a community level, we designed a cluster randomized trial to implement and evaluate a theory-based CM intervention conducted and allocated at the community level that addresses known social barriers to engagement in HIV care. We aim to determine whether the intervention decreases undiagnosed infections and improves linkage to and retention in HIV care among adults aged 18–49 years in the intervention communities as compared to adults 18–49 in the control communities, with the overall goal of reducing new HIV infections and improving health outcomes of those living with HIV. We also aim to understand the mechanisms of action of this mobilizing program through our community surveys and determine what comprises the ideal format for delivery of the program. This manuscript describes the trial protocol.

## Methods/design

### Study site and population

This study is being conducted in the Agincourt sub-district of Bushbuckridge in rural Mpumalanga province of South Africa—the area is covered by a health and socio-demographic surveillance system (Agincourt HDSS) established in 1992 and run by the Medical Research Council/Wits University Rural Public Health and Health Transitions Research Unit (Agincourt). Through the annual household and vital events update, the unit maintains a detailed database and sampling frame, including geo-coding, of over 20,000 households and over 115,000 resident individuals living in 31 fully enumerated villages, 15 of which are participating in this study [50]. The current study focuses on HDSS residents aged 18–49 years.

Population-based HIV prevalence among the adult population 15 years and above in the Agincourt HDSS was 19.4% in 2010–2011 and peaked at over 45% among 35–39-year olds [51]. HIV testing and clinical care for HDSS residents is provided by nine public health facilities and one public-private-partnership community health center located within the study area. These ten facilities serve multiple communities throughout the HDSS. As community members commonly receive services outside their village, the study includes monitoring HIV services provision at all ten health facilities (Fig. 1).

**Fig. 1 Fig1:**
[figure not shown]
Map of the Agincourt Health and Socio-Demographic Surveillance System (Agincourt HDSS) and surrounding area

### Specific aims

The CM intervention is being evaluated by comparing uptake of testing, linkage, and retention in care in 15 communities randomized to either an intervention condition (*n* = 8) or a control condition (*n* = 7) located within the Agincourt HDSS. To measure outcomes in each village, we are linking the longitudinal population-based HDSS data to a health facility-based electronic clinical tracking system used in all HDSS health facilities. The linkage of the health facility and census data allows us to establish an open cohort of approximately 34,000 18–49-year-old residents that includes exposure data (village of residence) as well as outcome data (HIV-related clinical care). Using these data, we will evaluate the effects of the CM intervention by village randomization arm as well as characterize the HIV care cascade in a high prevalence population. We will also evaluate the conceptual model, including the hypothesized CM processes [52], through community surveys to monitor intervention exposure and community level change using validated CM measures [53]. The specific aims of the study include:

#### Aim 1, testing

To determine whether uptake of HIV testing among residents of communities receiving a community mobilizing intervention is higher than residents of control communities.

#### Aim 2, linkage

To determine whether linkage to care is higher among residents of intervention versus control communities as measured by (a) proportion of those testing HIV positive who complete CD4 staging within 3 months of diagnosis and (b) the proportion of those eligible for treatment who initiate ART within 3 months of CD4 staging.

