#### Aim 3, retention

To determine whether retention in care is higher among people in intervention compared to control communities, including (a) proportion of ART initiated patients not defaulting from care (with no more than a 90-day gap in treatment during 12 months) and b) those ineligible for ART returning for CD4 staging at 6-month intervals.

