### Study measures

#### Primary exposure

Residence in an intervention or control community is the primary predictor variable for all analyses. Community of residence will be determined using the HDSS data. Household and vital events data are updated annually and include births, in- and out-migrations and deaths. Although few individuals are expected to move within the study area over the course of the study, for those who do move, exposure will be determined dynamically over the course of the study such that individuals will be considered exposed if they were resident in an intervention community in the time period immediately prior to the outcome. Table 2 summarizes the quantitative data elements that include exposures, outcomes, mediators, and social and demographic co-variates.

**Table 2 Tab2:** Summary of quantitative data elements

Domain	Instrument/measure	Data source and frequency
Primary exposure		
Village	Village of residence (binary; intervention vs. control village)	HDSS-annual
Primary outcomes		
Testing uptake (aim 1)	Binary: tested/untested past 12 months, among HIV-negative or unknown status residents	Electronic health facility records-ongoing
	Binary: known HIV status–either confirmed positive or tested within the last 12 months	Electronic health facility records-ongoing
Linkage to HIV care (aim 2)	Binary: received baseline CD4 results and evidence of follow-up care (additional CD4, viral load, or treatment initiation) within 3 months of testing HIV positive	Electronic health facility records-ongoing
	Binary: treatment initiation within 3 months of positive diagnosis among those eligible for ART	Electronic health facility records-ongoing
Retention in HIV care (aim 3)	Binary: HIV patients on or initiating ART who have no more than a 90-day gap in medication received in the 12-month period (no defaulting).	Electronic health facility records-ongoing
	Binary: HIV patients not ART eligible^a^ who have a repeat CD4 test 6–12 months after initial CD4	Electronic health facility records-ongoing
Meditator/mechanism		
Community mobilization	Six domains of community mobilization measure [53]	Population-based surveys (years 1 and 5)
Covariates		
Demographics	Age, SES, gender, migration status	HDSS-annual
Social norms	Stigma [81]; gender norms [41]; community support for HIV testing and treatment [53]	Population-based surveys (years 1 and 5)
Secondary outcomes		

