### Analysis

One-way frequency tables for all variables and measures of central tendency and variability for continuous variables will be generated to perform range checks, quantify the amount of missing data, and yield valuable descriptive findings that will further characterize the care cascade in the study population. These analyses will also be stratified by randomization group (i.e., intervention versus control) using cluster-based two-group comparison methods (e.g., Rao-Scott chi-square) to check the equality of intervention and control group covariates at baseline. If the intervention and control groups are found to differ significantly at baseline on one or more covariates (e.g., gender; mean age of village residents), we will use methods based on the Rubin causal model (e.g., propensity scores, targeted maximum likelihood estimation, double-robust estimation) [60] to obtain the desired marginal effect estimates under the counterfactual assumption of balanced groups [61–65]. We will assess and document the amount of missing data from health facility systems and community surveys. In the unlikely event that a variable has >5% of missing data, we will address incomplete data via either inverse probability of censoring weights (IPCW) or use multiple imputation (MI) [66], as it makes the relatively mild assumption that incomplete data arise from a conditionally random (MAR) mechanism rather than the completely random process (MCAR) assumed by ad hoc methods such as list-wise data deletion [67]. For MI, auxiliary variables will inform multiple imputations to increase the likelihood of meeting the MAR assumption [68, 69].

We hypothesize that following the intervention, for the intervention community relative to the control community residents:The odds of HIV testing will be higher (specific aim 1);The odds of linkage to care will be higher (among those HIV-infected; specific aim 2);The odds of retention in care will be higher (among those HIV-infected; specific aim 3); andThe community means of the six domains of community mobilization will be higher and associated with individual level outcomes (specific aim 4).

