Primary analyses will follow an intent-to-treat (ITT) approach and will be unadjusted except for intervention group, and, for longitudinal analyses, time, and the group-by-time interaction. Individual will be the unit of analysis. Our principal interest is to estimate the marginal or population-average effect of the intervention on each outcome rather than the effect for a hypothetical average subject [70]. Moreover, within-subject correlations among outcomes are considered nuisance parameters rather than quantities of interest to be modeled explicitly. Accordingly, generalized estimating equations (GEE) will be used to perform the proposed primary longitudinal analyses, including planned time-averaged comparisons of post-baseline measurements across the intervention and control arms to test primary hypotheses 1–3 listed above. Alpha will be set at .05 for these planned comparisons of each separate outcome. Any additional post-hoc comparisons (e.g., paired comparisons of the control and intervention arms at each time point) will maintain a nominal alpha level of .05 through the use of simulation-based stepdown multiple comparison methods [71]. GEE accounts for correlation of repeated measurements from the same research participant via computation of a working correlation matrix and yields the desired marginal population-average effect estimates [72]. Village ID will be included as a nested fixed effect or via alternating logistic regression (ALR) to account for clustering of persons nested within villages. GEE estimates are consistent even if the correlation structure is mis-specified, though GEE’s statistical efficiency improves as the working correlation structure more closely approximates the actual correlation structure [73]. Thus, several suitable working correlation structures will be considered (e.g., unstructured, AR(1), exchangeable) [74]. The QIC or a similar statistic will be used to select the final working correlation structure [75]. Robust Huber-White “sandwich” standard errors will be used to obtain correct inferences even if the chosen correlation structure remains slightly mis-specified.

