## Discussion

The Tsima ra rihanyu program is built on a theory-based CM model that aims to remove the major social barriers to successful participation in the HIV care cascade and ultimately activate the promise of TasP. The cluster-randomized research design and the linked data sources including a measure of CM administered through community surveys will provide a robust structure within which to evaluate the intervention and simultaneously, provide insight as to the mechanisms of action in improving testing, linkage, and retention. In addition, because the study is embedded in an HDSS, we will have true denominators for our estimates and will therefore generate much needed population-based data contributing to improved characterization of the HIV care cascade. These data will also provide an opportunity to optimize program design through targeting groups with the greatest need of care support.

This study focuses on community approaches to improving uptake of HIV testing and care and is not focused on directly mitigating health facility-level barriers to care, including quality of HIV care, drug stock-outs, long wait times, or lack of confidentiality. However, the intervention design does not prohibit mobilization teams and/or CATs to plan activities at the clinics or with the clinics and does encourage partnerships with clinic leadership as primary stakeholders in improving the care cascade. Because intervention and control populations will be accessing the same group of clinics and because varied quality of care across the health facilities and different levels of involvement in the intervention by health facility could affect the study outcomes, the team agreed that any intervention activities that target health facility leadership or address health facility services will be conducted in all study health facilities, in order to ensure that potential effects of clinic-based activities will be consistent across all villages. Additionally, to address basic health facility functionality, and mitigate any health facility-specific influence on study outcomes, the team has partnered with the local PEPFAR partner, Right to Care, to work with all study area health facilities to ensure that best practices for HIV prevention, testing, care, and treatment are in place and that monitoring systems and data capture are standardized and that supplies, including test kits and drugs, are available.

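### Aim 2 compares linkage only among people diagnosed after randomization, so the contrast mixes any effect on linkage with a change in who is diagnosed

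*Protocol article*

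**What the plan says.** The first aim is "To determine whether uptake of HIV testing among residents of communities receiving a community mobilizing intervention is higher than residents of control communities" (Aim 1, testing). The Background adds that fewer undiagnosed infections are intended, and Table 3 (Power) sets 35% tested as the current estimate and 60% as the intervention target.

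Aim 2 then measures linkage in two groups that exist only after testing:
- the "proportion of those testing HIV positive who complete CD4 staging within 3 months of diagnosis";
- "the proportion of those eligible for treatment who initiate ART within 3 months of CD4 staging".

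Table 2 words the two outcomes somewhat differently but also conditions on a positive test or on ART eligibility. The matching hypothesis reads "The odds of linkage to care will be higher (among those HIV-infected; specific aim 2" (Analysis).

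For retention, Aim 3 refers to the "proportion of ART initiated patients not defaulting from care", and Table 2 gives the wider group of "HIV patients on or initiating ART who have no more than a 90-day gap in medication received in the 12-month period".

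On method, "Primary analyses will follow an intent-to-treat (ITT) approach", unadjusted except for arm and, in longitudinal models, time and their interaction. The one planned correction for imbalance is triggered by baseline covariate differences. The limitations paragraph of the Discussion covers migration, loss to follow-up and the unknown number of residents living with HIV. It does not cover selection into the diagnosed group.

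**The concern.** Randomization makes the residents of the two arms comparable. It does not make those who test positive comparable if the intervention changes who tests, and here changing who tests is the purpose of Aim 1. The Background says that stigma delays testing and treatment and that men start ART less often and later. People brought in by mobilization may therefore link at a different rate from people who would have tested anyway.

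The Aim 2 contrast then has two sources: a change in linkage among people who would test regardless, and a change in the make-up of the diagnosed group. The planned analysis cannot separate them. The practical danger is that the intervention raises both testing and the number of people linked, yet shows no difference, or a fall, on the linkage outcome.

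**Working it through.** **The plan's own figure.** Table 3 gives a minimum detectable difference of 18 points for CD4 staging, from 65%. Inputs from the Power section: 449 new cases a year, intra-class correlation 0.05, alpha 0.05 (taken as two-sided), power 0.80, 8 and 7 villages.
- Cases per village: m = 449/15 = 29.9.
- Design effect: 1 + 28.9 × 0.05 = 2.45.
- Solve d = (1.96 + 0.84) × √[p0(1−p0) × 2.45/(7m) + p1(1−p1) × 2.45/(8m)] with p0 = 0.65 and p1 = p0 + d. This gives d = 17.9 points, which agrees with the 18 stated.

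**Set-up for the selection effect.** Split HIV-positive residents into usual testers (would test anyway, 35%) and extra testers (test only because mobilized, 60% − 35% = 25%).
- From Table 3: testing 35% and 60%; linkage 65%.
- Assumed: HIV-positive residents test at the Table 3 rates; extra testers link at a rate q between 35% and 85%.

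With a true gain g among usual testers:
- linkage among the diagnosed, intervention arm = [0.35 × (0.65 + g) + 0.25 × q]/0.60;
- share of HIV-positive residents linked = 0.35 × (0.65 + g) + 0.25 × q, against 0.35 × 0.65 = 22.8% in control.

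**No effect among usual testers (g = 0).** The contrast reduces to (0.25/0.60) × (q − 0.65).
- q = 35%: −12.5 points
- q = 45%: −8.3
- q = 55%: −4.2
- q = 65%: 0
- q = 75%: +4.2
- q = 85%: +8.3

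If testing rises only to 45%, the multiplier is 0.10/0.45 and the range for q from 35% to 85% is −6.7 to +4.4 points.

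**A real gain, masked.** With g = +10 points and q = 45%: (0.35 × 0.75 + 0.25 × 0.45)/0.60 = 0.375/0.60 = 62.5%. Against 65% this reads as −2.5 points, while the share of HIV-positive residents linked rises from 22.8% to 37.5%. With g = +18, the stated detectable difference, the contrast is zero when q = (0.39 − 0.35 × 0.83)/0.25 = 39.8%.

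**Retention.** Take 3 years of new initiators as 449 × 3 × 0.65 × 0.60 = 525 in control and 525 × 60/35 = 901 under intervention, both scaled to the whole area. Treating every staged patient as eligible is an assumption. Table 3 gives 50% retained; suppose the 375 extra initiators are retained at 20% to 80%.
- New initiators alone: (375/901) × (±0.30) = ±12.5 points.
- With the roughly 6000 patients already on ART in 2014: (375/6901) × (±0.30) = ±1.6 points.
- If only half of those 6000 live in study villages: (375/3901) × (±0.30) = about ±3 points.

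The stated detectable difference for retention is 19 points.

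**The case against.** Aim 2 openly chooses cascade-step measures. Such proportions are standard, their denominators are stated, and supplementary denominators could sit in an analysis plan that is not shown. That stands as a reason to keep the measures. It does not remove the problem, because the article itself fixes these denominators as primary and specifies the unadjusted contrast by arm.

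The size rests on assumptions, and this objection stands. No linkage rate for extra testers is given. New diagnoses need not scale with testing either: the Table 2 outcome counts any test in 12 months, repeats included, and the Power section assumes only that at least a third of those tested each year are new to testing in the study period. Hence the ranges and the smaller testing rise.

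A reader might go further in four ways that the documents do not support:
- *Retention is equally compromised.* The Table 2 denominator includes patients already on ART, most of whom entered care before the intervention, so the shift is small.
- *A true loss could readily look like a gain.* That needs linkage to fall among usual testers and extra testers to link better than they do. Nothing in the article suggests either, and the Background leans the other way on extra testers.
- *A resident-based measure pointing the same way would confirm a linkage effect.* It would not. With no effect among usual testers and q = 85%, the conditional contrast is +8.3 and the share linked rises from 22.8% to 0.2275 + 0.25 × 0.85 = 44.0%. Both rise, but linkage among usual testers has not changed.
- *The plan contradicts itself on denominators.* The hypothesis wording about the HIV-infected can be read as shorthand. The remark that "because the study is embedded in an HDSS, we will have true denominators for our estimates" (Discussion) concerns characterizing the care cascade. The article also has resident-level measures: known HIV status among the primary outcomes and viral suppression among the secondary ones.

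**Conclusion.** The concern holds for Aim 2. The linkage contrast is conditional on groups that the intervention is designed to enlarge, and nothing in the article corrects for this or limits the interpretation. On the Table 3 testing target, selection alone could move the contrast by −12.5 to +8.3 points, and with a testing rise to 45% by −6.7 to +4.4, against a detectable difference of 18. These figures assume that HIV-positive residents test at the Table 3 rates and that extra testers link at 35% to 85%. The true direction and size are unknown.

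The likeliest harm is a masked gain. For retention the concern is limited to new initiators; with patients already on ART included it is about 1.6 points under the inputs shown. The point should be corrected because it bears on what Aim 2 can conclude. It does not invalidate the cascade measures.

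**What to change.** - Keep the conditional proportions as cascade steps.
- Beside them, pre-specify the proportion newly diagnosed and linked within 3 months, over residents aged 18–49 not known positive at trial start, or over all residents aged 18–49. Fix known status at trial start, because status at the start of later windows can itself drift by arm.
- State that this population version measures the combined effect on testing and linkage. State also that the conditional contrast alone will not be read as the intervention's effect on linkage if testing or diagnosis differs by arm. Do not require the two versions to agree in direction, since the population version tends to rise whenever testing rises.
- For retention, add a sensitivity analysis in patients on ART before 1 August 2015, when intervention activities began.

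The cost is a few extra models on records that the plan already creates for every resident. The population rates will be small and will vary with village HIV prevalence, which is not among the listed balancing covariates, across only 15 clusters. Clinic capture began between June and August 2015 at nine clinics and in July 2016 at the tenth, so status before launch will depend largely on dates taken from patient files. The all-residents denominator avoids that dependence.
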